##### Sequential yoga poses

Sequential yoga poses focusing on the myofascial continuum of the UQR will be done in the following sequences: triangle pose, extended side angle pose, seated eagle pose, cow face pose, child pose, reverse prayer pose, camel pose, bow pose, and child pose. Each posture will be held for a period of 5 breath cycles, which will be progressed by increasing the number of breathes during these asanas [32–34]. The interventions’ details are given in Additional file 3: TIDieR Intervention group [37, 38]. The patient’s home-based yoga poses are illustrated in Additional file 5: Yoga poses- Information leaflet [32–34].

#### Intervention adherence

Steadfast adherence to exercise-based interventions enhances the effectiveness of the interventions in rehabilitation. Studies have shown that robust exercise adherence may improve neck and back pain patients [49, 50]. The patients will be explained the significance of adhering to study guidelines of home-based rehabilitation exercises and the importance of proper form and exercise execution. The patients will also be advised to contact the investigator on events of any acute flare-up of symptoms.

Reminders via e-mail at regular intervals and Google forms will be sent. Participants will give feedback regarding the intensity, frequency, and duration of their exercise training and the difficulties in performing exercises, improving the adherence and ensuring their participation in the study. These data will be collected once in 2 weeks during the unsupervised exercises following four treatment sessions until the end of 3 months. The investigator will provide leaflets (Additional files 4 and 5) depicting the entire exercise regimen and daily logbook, which will act as reminders if the participants do not have access to the e-mails.

#### Interventions—concomitant care

The concomitant use of NSAIDs, muscle relaxants, and analgesics will be based on the physician’s recommendation and at patients’ discretion. The medications used will be recorded.

### Outcomes

#### Primary outcome measure

Numeric pain rating scale (NPRS).

##### Numeric pain rating scale

The NPRS is a valid and reliable PROM used for MNP patients. The NPRS has a moderate reliability (ICC = 0.67; [0.27 to 0.84]) [51]. Participants will indicate the intensity of neck pain in the past week. A reduction of 1 point in the NPRS was represented as the minimal clinical important difference (MCID) in patients with chronic musculoskeletal pain [52].

Baseline values will be collected from participants before the first treatment session. Also, the patient’s expected improvement in the NPRS scale following interventions will be assessed. This primary outcome data will be further collected during the 2nd, 3rd, and 4th treatment sessions and the 3rd month and 6th month following the first treatment session. The principal analysis will be performed for changes from baseline to 3- and 6-month follow-up and between the treatment sessions. It will be reported as the difference in the change in the mean between the groups. During analysis, a change score of two in the NPRS scale will be considered as MCID as this score is associated with “much better” improvement [52].

#### Secondary outcome measures

Patient-specific functional scale (PSFS)Oculomotor control tests
Smooth pursuit neck torsion (SPNT) test, saccades using videonystagmographyNear point convergence (NPC) test using RAF rulerFear-avoidance belief questionnaire—physical activity (FABQ-PA)Myofascial stiffness using myoton-proElbow extension ROM during upper limb neurodynamics test 1 (ULNT1) using a goniometer

##### Patient-specific functional scale

The PSFS quantifies the activity limitation in patients where the three most challenging and painful activities will be identified. The total score is the summation of all the activity scores divided by the total number of activities. The minimum detectable change (MDC) for an average rating is 2 points, and the MDC for a single activity score is 3 points [53]. Baseline values will be collected from participants before the first treatment session. Also, the patient’s expected improvement in the PSFS following interventions will be assessed.

The primary analysis will be done for changes from baseline to the last treatment session and 3rd- and 6th-month follow-ups and will be reported as the change in means between the groups.

#### Oculomotor control tests

##### Smooth pursuit neck torsion test

The smooth pursuit neck torsion (SPNT) test assesses the smooth pursuit eye movements with a torsioned neck using videonystagmography (VNG) [54]. In this test, participants will be instructed to follow the target with the eyes without blinking as well as keeping the head still. Initially, smooth pursuit measurement will be performed with the neck and trunk in a neutral position followed by the torsioned position of the trunk to 45° by rotating the trunk on the one side. The same procedure will be repeated, and measurements will be done by rotating the trunk on the opposite side [54, 55]. The SPNT test parameter is the difference between the average gain in the neutral and torsioned positions [25–27, 56].

##### Saccades

Saccades will be measured using VNG, which are rapid voluntary eye movements primarily directed towards stationary targets. In saccades, both eyes move simultaneously between two or more phases of fixation in the same direction. The parameters to be measured in saccades include peak velocity, measured in degrees/second, and latency in milliseconds [25, 26, 54].

##### Near point convergence test

NPC will be measured using an RAF ruler to identify the presence of any convergence insufficiency. Convergence insufficiency (CI) measured by near point convergence (NPC) may be a feature in MNP, thus measuring NPC with neck torsion may differentiate the cervical cause of CI. Giffard et al. have investigated the repeatability and reliability of NPC measurements in neutral and torsion position between the neck pain patients and controls using a Royal Airforce (RAF) ruler. A significant NPC torsion difference was demonstrated in participants with NP compared to controls (*P*=0.01). No significant differences were seen for NPC values in neutral (*P*=0.73). High inter-rater reliability (ICC=0.95) and repeatability (ICC=0.84) was obtained [57].

#### Fear Avoidance Beliefs Questionnaire (FABQ)

The fear-avoidance model (FAM) describes chronic pain development as a psychological process [58]. Although fear-avoidance beliefs (FAB) is considered a key variable in predicting, chronic low back pain (CLBP) FABQ was associated with pain and disability in patients with MNP in increasing order of fear-avoidance beliefs (FAB). FABQ includes a four-item scale, which measures the FAB about physical activity (FABQ-PA), and a seven-item scale, which measures the FAB about work (FABQ-W). The questions of the FABQ refer to “neck pain” instead of low back pain to address the participants with MNP [59]. Higher scores in the FABQ indicate greater levels of fear-avoidance beliefs. Although the association between FAB, pain, and disability in neck pain patients is weaker than in the LBP patients, studies have shown no significant difference in FAB between patients with neck and low back pain. Authors have shown that both FABQ work-related subscales have a substantial relationship with returning to work capability in patients with MNP [59, 60]. FABQ-PA scores include a total score and can be considered as an elevated score when it is 15 or above [58]. Principal analysis will be conducted for changes from baseline to the 3rd- and 6th-month follow-ups and will be reported as the change in the mean between groups. Lee et al. have demonstrated a very good content validity and test-retest reliability of FABQ questionnaire (ICC= 0.81)/(Cronbach’s alpha coefficient= 0.90) [61].

#### Myofascial stiffness

The viscoelastic properties include elasticity (log decrement), stiffness (N/m), and tone (Hz). These mechanical properties will be measured by using Myotonpro on the following muscles: masseter, temporalis, sternocleidomastoid, upper Trapezius, biceps brachii, infraspinatus, and teres minor. Myoton Pro induces oscillation on the skin surface, thus helps in determining the viscoelastic properties of the soft tissues of UQR [62, 63]. The primary analysis will be conducted for changes from baseline to the final treatment sessions and 3rd-month follow-up. The results will be reported as the change in the means between groups.

#### Elbow extension ROM during upper limb neurodynamics test

The mechanosensitivity of the upper limb neural structures may occur due to the nerves’ impaired mobility with their adjacent mechanical interface. The elbow extension ROM (EEROM) is the point in the elbow extension range while performing ULNT1, where the subject experiences pain or discomfort. This degree of elbow flexion will be measured using a standard goniometer [13, 64]. The analysis will be performed for changes from baseline to 3- and 6-month follow-up and between the treatment sessions. The results will be reported as the difference in the change in the mean between the groups.

#### Participant’s timeline

The schedule of enrolment, interventions, and assessments of the participants are outlined in SPIRIT Table 1.

**Table 1 Tab1:**
[figure not shown]
Participants’ timeline. Schedule of enrolment, interventions, and assessments

*Summary of measures to be collected [SPIRIT guidelines 2013]

*NPRS* numerical pain rating scale, *PSFS* patient-specific functional scale, *FABQ* fear avoidance behavior questionnaire, *SPNT* smooth pursuit neck torsion test, *NPC* near point convergence, *EEROM* elbow extension range of motion

#### Sample size

The sample size is estimated based on the primary outcome NPRS. The threshold for MCID in MNP patients with and without UE symptoms is 2.2 and 1.5, respectively [51], whereas the MCID for NPRS in patients with chronic musculoskeletal pain is 1 [52]. Thus, MCID is considered as one in order to have a substantial sample size in this trial.
$$ n=\kern0.5em \frac{2\ \left({Z}_{1-\alpha /2}+{Z}_{1-\beta}\right).\kern0.5em {\sigma}^2\left[\ 1+\left(m-1\right)\rho \right]}{m{d}^2} $$

*d* - MCID = 1

Z_1-α/2_ = 1.96 at *α*=0.05

Z1-β = 1.28 at 90% power

*m* = Number of time points/follow-ups = 5

*ρ* = Intraclass correlation = 0.4

$$ n=\frac{2\times {\left(1.96+1.28\right)}^2\times 2.{5}^2\times 2.2}{5\times {1}^2}=\mathbf{58} $$

Accounting for dropout rate/non-response rate

*N*^*x*^ = *N*/1 – dropout rate; for 10% dropout rate

Required sample size = **64** participants/group.

Total number of participants in the trial = **128**

To detect a difference of one on the NPRS scale (pain intensity) between the groups assuming a standard deviation of 2.5 at a 5% level of significance and 90% power and 10% dropout, the minimum number of participants required in each group is **64**.

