#### Statistical methods

For all the continuous primary and secondary outcomes listed in Table 2, where repeated measurements are to be taken, repeated measures ANOVA will be used. The Student’s *t* test will compare the intervention group (IG) and the control group (CG) during interim assessments. The difference in means will be used for the analysis of continuous variables. All statistical tests will be carried out at a 5% (two-sided) significance level. All analyses will be carried out using the R software, which is open-source software. Patients will be stratified into group 1 ages 18–30 and group 2 ages 31–45. Subgroup analysis will be done based on these groups.

**Table 2 Tab2:** Summary of reporting outcome measures

Variables/outcomes	Methods of analysis

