***Primary outcome measure***	
NPRS (change of pain score during last week) [***∆t***_***0***_ ***→ t***_***3m***_***→ t***_***6m***_ ]	Repeated measures ANOVA

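### The stated 90% power is for a mean over five NPRS scores with no baseline term; on the protocol's inputs the change-from-baseline analyses it names have less

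*Protocol article*

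**What the plan says.** The sample size section of the protocol article gives its aim as "To detect a difference of one on the NPRS scale (pain intensity) between the groups". The calculation takes an SD of 2.5, a 5% test, 90% power and a loss of 10%. Its other inputs are "Number of time points/follow-ups = 5" and "Intraclass correlation = 0.4". The result is 58 per group, or 64 after dropout (128 in total). The abstract announces 160.

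The five time points match the five post-baseline NPRS assessments in the outcome section: treatment sessions 2, 3 and 4, and months 3 and 6.

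Two places describe the primary analysis:

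- Table 2 lists "NPRS (change of pain score during last week" and so on, over baseline, month 3 and month 6, by repeated measures ANOVA.
- The NPRS outcome section bases the principal analysis on changes from baseline to 3 and 6 months and also between treatment sessions, and adds: "It will be reported as the difference in the change in the mean between the groups".

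The statistical methods section states: "All statistical tests will be carried out at a 5% (two-sided) significance level". No power is given for either description of the primary analysis.

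**The concern.** The formula treats the outcome as a mean of five scores. Averaging five correlated scores cuts the variance to about half that of one score, and that reduction is what produces a sample size of 58. Two features of the named analysis work the other way. It subtracts baseline, which adds variance when the correlation is as low as 0.4. In Table 2 it also uses two follow-up visits rather than five.

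The formula further credits every visit with the full 1-point difference. By Table 3, three of the five scores are taken before sessions 2, 3 and 4, that is, after only one, two or three sessions.

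At stake is how a null result would be read. It could be reported as a negative finding from a trial with 90% power, when the analysis that produced it may have had much less.

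**Working it through.** **Inputs.** All are from the sample size section unless noted: difference d = 1; SD σ = 2.5, so σ² = 6.25; ρ = 0.4; m = 5; z = 1.96 and "1.28 at 90% power". Evaluable numbers per group are 58 (that section) and 72 (160 in the abstract gives 80 per group, × 0.9).

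**Assumptions.** σ is the SD of a single score, ρ is the same for every pair of visits including baseline, and the full 1-point difference holds at each follow-up visit used.

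**The plan's own figure.** The printed formula omits the square on the sum of the z values. The worked line includes it, so I treat the omission as typographical.

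- As printed, with 2.2: 2 × 3.24² × 6.25 × 2.2 / 5 = 57.7, so 58.
- With the stated inputs: 1 + (5 − 1) × 0.4 = 2.6, and 2 × 3.24² × 6.25 × 2.6 / 5 = 68.2, so 69; 69 / 0.9 = 76.7, so 77 after dropout.
- The value 2.2 corresponds to ρ = 0.3 with m = 5, or to m = 4 in the bracket with 5 kept in the denominator.

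**Power by contrast.** For a per-patient variance of σ² × f, power = Φ(d / √(2σ²f/n) − 1.96).

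| Contrast | f at ρ = 0.4 | n = 58 | n = 72 |
|---|---|---|---|
| Mean of five follow-up scores (as sized) | (1 + 4ρ)/5 = 0.52 | 85% | 91% |
| Change to one month | 2(1 − ρ) = 1.20 | 50% | 59% |
| Change to mean of months 3 and 6 | (1 + ρ)/2 + 1 − 2ρ = 0.90 | 62% | 72% |
| Change to mean of all five visits | 0.52 + 1 − 2ρ = 0.72 | 72% | 81% |
| Baseline-adjusted mean of months 3 and 6 | (1 + ρ)/2 − ρ² = 0.54 | 83% | 90% |

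Example, third row at n = 72: √(2 × 6.25 × 0.90 / 72) = 0.395; 1/0.395 = 2.53; Φ(2.53 − 1.96) = 0.72.

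**Group-by-time F test.** With a group difference of 0, 1, 1 at baseline, month 3 and month 6, λ = (n/2) × (2/3) / (6.25 × 0.6), which is 5.16 at n = 58 and 6.4 at n = 72. The noncentral F with 2 numerator df gives 51% and 61%. Over all six occasions, with the full effect from session 2, 2/3 becomes 5/6 and there are 5 numerator df; λ is 6.44 and 8.0, and power is 46% and 56%.

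**Size for 90% power at ρ = 0.4.** n = 2 × 10.4976 × 6.25 × f:

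- change to one month: 157.5, so 158 evaluable;
- change to the mean of months 3 and 6: 118.1, so 119;
- baseline-adjusted mean of months 3 and 6: 70.9, so 71, and 71 / 0.9 = 78.9, so 79 randomised.

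**Sensitivity (values at n = 58 / n = 72).**

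- ρ = 0.5 (assumed): change to one month 58% / 67%; change to the two-month mean 70% / 79%.
- ρ = 0.67 (assumed): change to the two-month mean, f = 0.495, 86% / 93%; the five-visit mean as sized, f = 0.736, 71% / 80%.
- 2.5 read as the SD of change, with 0.4 as the correlation between changes: one month, f = 1, 58% / 67%; two-month mean, f = 0.70, 73% / 82%.

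**The case against.** The strongest counter-argument is that the document does not confine the principal analysis to months 3 and 6. The outcome section includes changes between treatment sessions, and Table 4 reports NPRS differences between successive visits. A reader of Table 2 alone might infer that three of the five visits that supply the power are left out of the primary analysis. The documents do not support that as a flat statement: Table 2 and the outcome section differ, and the primary contrast is unsettled. Including the session visits still does not bring 90% under the main assumptions. Change to the mean of all five visits has 72% / 81%, and the six-occasion interaction test has 46% / 56%. The Table 4 entries are single-interval contrasts, not a five-visit average.

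A second argument is that 2.5 and 0.4 may describe change scores, since the abstract defines the outcome as a change in NPRS. The document does not say. On that reading the formula would size a mean of five changes (85% / 91% with f = 0.52), but neither description of the primary analysis names that average. The month 3 and 6 contrasts would still have only 58–73% / 67–82%.

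A third argument is dependence on ρ, and it stands. At 0.67 the two-month change would exceed 90% at 72 per group. The five-visit mean would then fall to 71% / 80%, so that value does not support the calculation as printed. The protocol's own value is 0.4.

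Finally, covariate adjustment may be left to an analysis plan that is not shown. That is fair; the point here is that the stated power and the stated analysis disagree.

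**Conclusion.** The concern holds in limited form. The 90% power is calculated for a mean of five scores without baseline and does not apply to the change-from-baseline analyses named in Table 2 and the outcome section. On the protocol's inputs, the month 3 and 6 change contrasts have 50–62% power at 58 evaluable per group and 59–72% at 72. These are two ranges at two sample sizes and should not be merged into one.

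Part of the shortfall at 58 has another cause: with 2.6 in place of 2.2, even the five-visit mean has about 85%, so 90% should not be taken as correct for that contrast either.

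The mismatch itself is plain from the text. The exact power figures are less certain, because they rest on a single-visit SD of 2.5, an equal correlation of 0.4 across all visits, and raw change scores.

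A reader might also infer that 160 patients are too few. That does not follow: the same data analysed with baseline adjustment over months 3 and 6 give about 90% at 72 evaluable per group.

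**What to change.** Reconcile the sample size section, the NPRS outcome section and Table 2 on one primary contrast, say whether 2.5 and 0.4 refer to single scores or to changes, correct the factor, and state the power for that contrast.

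One option that fits the announced size is the baseline-adjusted NPRS difference averaged over months 3 and 6. It needs 71 evaluable, about 79 randomised, per group (158 in total, against 160). It is mildly sensitive to ρ: at 0.3 the factor is 0.65 − 0.09 = 0.56 and power at 72 is about 89%. Other contrasts are defensible if their own power is given.

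If the unadjusted change analysis is kept, restate its power: for the two-month mean, about 72% with 160 recruited and 62% with 128.

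The cost is a few reworded lines and, if change scores are kept, a less favourable stated power. No extra patients or visits are needed.

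### The sample-size line uses 2.2 for a factor that its listed m = 5 and ρ = 0.4 make 2.6, so 58 evaluable (64 randomised) per group at 90% power does not follow from the stated inputs

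*Protocol article*

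**What the plan says.** The Sample size section (Protocol article, Methods) sizes the trial on the NPRS with a repeated-measures formula. The number per group is 2 times the squared sum of the two normal quantiles, times σ² and the factor [1 + (m − 1)ρ], divided by m·d². The symbolic version omits the square on the sum of quantiles, but the numeric line includes it.

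The listed inputs are:
- Significance level: "1.96 at *α*=0.05". The Statistical methods section confirms that it is two-sided: "All statistical tests will be carried out at a 5% (two-sided) significance level".
- Power: "Z1-β = 1.28 at 90% power".
- Repeated measurements: "Number of time points/follow-ups = 5".
- Correlation: "Intraclass correlation = 0.4".
- Difference: one NPRS point ("MCID is considered as one in order to have a substantial sample size in this trial").
- Spread: "assuming a standard deviation of 2.5 at a 5% level of significance".

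The numeric line puts 2.2 in place of the factor, divides by 5 and reports 58 per group. This is inflated for 10% dropout to 64 per group and 128 in total. The section ends by stating that, "at a 5% level of significance and 90% power and 10% dropout, the minimum number of participants required in each group is" 64.

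Two other places give a different total. The Methods paragraph of the Abstract plans 160 patients, and Sequence generation sets out sixteen blocks of ten, which is also 160.

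**The concern.** The factor in the numeric line is not the one that the listed inputs produce, and the article does not explain 2.2. The figures 58, 64 and 128 and the 90% power claim all depend on it. This is the article's only justification of the trial's size on its primary outcome, and a reader cannot verify it as printed.

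If ρ = 0.4 is what the sponsor meant, the stated minimum is too small. A trial that stopped at 128 would then be described as having 90% power when its own formula gives about 85%, a type II error of about 15% against the claimed 10%.

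**Working it through.** **Inputs** (Sample size section): Z values 1.96 and 1.28, so (1.96 + 1.28)² = 3.24² = 10.4976; σ² = 2.5² = 6.25; d = 1; m = 5; ρ = 0.4; dropout 10%, applied as n/(1 − 0.1).

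**1. The printed figure.** n = 2 × 10.4976 × 6.25 × 2.2 / 5 = 57.7, so 58. Then 58/0.9 = 64.4, printed as 64 (65 if rounded up). The line is arithmetically correct once 2.2 is accepted. Because the printed 2.2 reproduces the printed 58, it is not a reading error in the extracted text.

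**2. The factor from the listed inputs.** 1 + (5 − 1) × 0.4 = 2.6, not 2.2.

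**3. Sample size with 2.6.** n = 2 × 10.4976 × 6.25 × 2.6 / 5 = 68.2, so 69 evaluable per group. Then 69/0.9 = 76.7, so 77 randomised per group and 154 in total. The gap from the printed figures is 11 evaluable or 13 randomised per group, too large to be rounding.

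**4. What would produce 2.2.** With m = 5, 1 + 4ρ = 2.2 gives ρ = 0.3. That single change reproduces both the factor and the result of 58, with the denominator still 5.

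**5. Power on this formula.** SE = √(2 × 6.25 × factor / (5n)) and power = Φ(1/SE − 1.96).

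| Evaluable per group | How it arises | ρ = 0.4 (factor 2.6) | ρ = 0.3 (factor 2.2) |
|---|---|---|---|
| 58 | 64 randomised, 10% dropout | 84.8% | 90.1% |
| 64 | 64 randomised, no dropout | 88.1% | 92.7% |
| 69 | 77 randomised, 10% dropout | 90.3% | 94.3% |
| 72 | 80 randomised (160 in total), 10% dropout | 91.4% | 95.1% |

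Example for 58 and ρ = 0.4: SE = √(12.5 × 0.52 / 58) = 0.335; 1/SE = 2.987; Φ(2.987 − 1.96) = Φ(1.027) = 0.848.

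**The case against.** The strongest objection is that the listed ρ, not the factor, may be the misprint. With ρ = 0.3 the whole numeric line is right, 58 evaluable per group gives about 90% power, and the only correction needed is to one input. This stands, and it limits the point. A reader might infer that 64 per group simply fails to deliver 90% power and that 2.2 must become 2.6. The article supports that only if ρ = 0.4 is the intended value, and it does not say which of the two figures is the slip. The contradiction remains, because 0.4 is the value stated and 0.3 is not.

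A reader might also infer that 2.2 came from using m = 4 in the factor. The text does not support this. The Numeric pain rating scale subsection schedules five post-baseline assessments (2nd, 3rd and 4th sessions, 3 months and 6 months), and the section lists m = 5 and divides by 5. Used consistently, m = 4 would give 2 × 10.4976 × 6.25 × 2.2 / 4 = 72.2, not 58.

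Next, 160 patients are planned elsewhere, and that is enough even with the factor 2.6. This is correct, and it confines the practical risk to recruitment that stops near 128. It does not repair the Sample size section, which still names 64 per group as the minimum and 128 as the total. The article does not say that 160 replaces 128.

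Other methods would need fewer patients. A one-sided 5% test would need (1.645 + 1.28)² × 12.5 × 0.52 = 55.6, so 56. A baseline-adjusted variance, with 0.52 − 0.16 = 0.36 in place of 0.52, would need 47.2, so 48. Neither applies: the tests are stated as two-sided, and baseline adjustment is neither the printed formula nor the repeated measures ANOVA that is planned.

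Finally, the formula averages five follow-ups, whereas Table 2 lists the NPRS change over baseline, 3 months and 6 months. The power figures here are therefore what this formula yields. They do not predict the power of the final analysis.

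**Conclusion.** The Sample size section contradicts itself. This is certain, and it can be checked by hand from that section alone: the listed m and ρ give 2.6, and the calculation uses 2.2.

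The consequence depends on which ρ was intended:
- **ρ = 0.4, as listed:** the requirement is 69 evaluable and 77 randomised per group (154 in total), and the printed design has about 85% power, roughly 5 points below the claim.
- **ρ = 0.3:** the size and power stand, and the listed ρ is wrong.

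Both cases assume m = 5, SD 2.5, a one-point difference, two-sided 5% and 10% dropout, all as printed. The documents do not support a flat statement that the trial is underpowered: the intended ρ is unresolved, and the 160 planned elsewhere gives about 91% on this formula even at ρ = 0.4. The sample-size statement still needs correction, because as printed its conclusion does not follow from its inputs.

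**What to change.** The sponsor should first confirm which ρ was intended.

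- **If ρ = 0.4 stands:** replace 2.2 with 2.6 and restate 69 evaluable and 77 randomised per group, 154 in total. Alternatively, keep 64 per group and restate the power as about 85% on this formula.
- **If ρ = 0.3 was used:** correct the listed value and justify it. The 58 then stands; 58/0.9 = 64.4 becomes 65 per group if rounded up.

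In either case, reconcile the 128 in the Sample size section with the 160 in the Abstract and Sequence generation, and say which is the recruitment target and why.

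The cost is a correction to the sample-size paragraph and one consistent total. No patients beyond the 160 already planned are needed, since 154 lies within it.
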